**Q5) A quelle fréquence mangez-vous des aliments salés comme popcorn, poisson salé etc.?**

- A) Au moins 1 fois par jour
- B) 3 à 6 fois par semaine
- C) 1 à 2 fois par semaine
- D) 2 à 3 fois par mois
- E) 1 fois le mois ou moins

**Q8) À quelle fréquence mangez-vous des légumineuses comme le haricot, petit pois, courge, sésame et les légumes vert comme feuille de manioc, épinards, fumbwa, oseilles ?**

- A) A tout moment pendant les grands repas
- B) Au moins 1 fois par jour
- C) 3 à 4 fois par semaine
- D) 1 fois par semaine
- E) Moins d'1 fois par semaine

**Q9) À quelle fréquence mangez-vous des graisses saturées comme la graisse de mouton, les jaunes d'œufs, le beurre, la margarine, etc.?**

- A) Au moins 1 fois par jour
- B) 3 à 6 fois par semaine
- C) 1 à 2 fois par semaine
- D) 2 à 3 fois par mois
- E) 1 fois le mois ou moins

**À quelle fréquence mangez-vous des aliments riches en graisse combiner aux aliments comme châteaux avec mayonnaise, charcuterie, omelette+ une boisson sucrée (l'une de chose peut manquer mais principalement les châteaux et boisson sucré fréquent ?**

- A) Au moins 1 fois par jour
- B) 3 à 6 fois par semaine
- C) 1 à 2 fois par semaine
- D) 2 à 3 fois par mois
- E) 1 fois le mois ou moins

**Q11) À quelle fréquence mangez-vous du beurre, de la crème, de la mayonnaise, etc.?**

- A) Au moins 1 fois par jour
- B) 3 à 6 fois par semaine
- C) 1 à 2 fois par semaine
- D) 2 à 3 fois par mois
- E) 1 fois le mois ou moins

**Q12) À quelle fréquence mangez-vous à l'extérieur de la maison (comme un mariage, une fête, une activité familiale, deuil etc.)?**

- A) Plus de 3 fois par semaine
- B) Plus d'une fois par semaine
- C) 2 fois par mois
- D) 1 fois par mois
- E) Moins d'1 fois par mois

**Q6) Combien de fois consommez-vous du sucre ou du miel dans votre thé ou café etc.?**

- A) Au moins 1 fois par jour
- B) 3 à 6 fois par semaine
- C) 1 à 2 fois par semaine
- D) 2 à 3 fois par mois
- E) 1 fois le mois ou moins

**Q7) À quelle fréquence mangez-vous des fruits et légumes?**

- A) A tout moment pendant les grands repas
- B) Au moins 1 fois par jour
- C) 3 à 4 fois par semaine
- D) 1 fois par semaine
- E) Moins d'1 fois par semaine

**Q13) Combien de jours d'exercice physique faites-vous par semaine?**

- A) Chaque jour
- B) 5 à 6 fois par semaine
- C) 3 à 4 fois par semaine
- D) 1 à 2 fois par semaine
- E) Jamais

**Q14) Combien de temps d'exercice faites-vous pour chaque session?**

- A) >40 minutes
- B) 30–40 minutes
- C) 20–30 minutes
- D) 20–10 minutes
- E) <10 minutes

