## Dietary evaluation

### **Diet diversity**

The minimum dietary diversity for women (MDD-W) developed by the Food and Agriculture Organization of the United Nations (FAO) is a dichotomous population-level indicator of whether participants have consumed at least five out of ten defined food groups the previous day. The MDD-W is used as a proxy to describe one important dimension of women's diet quality (micronutrient adequacy) in national and subnational assessments.

The general ten groups are presented below (list of foods contained by each group is presented in section 2 of guideline) :

1. Grains, white roots and tubers, and plantains
2. Pulses (beans, peas, and lentils)
3. Nuts and seeds
4. Dairy
5. Meat, poultry, and fish
6. Eggs
7. Dark green leafy vegetables
8. Other vitamin A-rich fruits and vegetables
9. Other vegetables
10. Other fruits

The threshold of this tool is: > 5 groups of food groups consumed indicates better micronutrient adequacy. The interpretation compromises that groups of women of reproductive age where a higher proportion consume food items from at least five of the ten food groups are likely to have higher micronutrient adequacy than other groups that have a lower proportion of women achieving the threshold of food items from at least five food groups. In other words, women of reproductive age who consume food items from five or more of the ten groups are also highly likely to consume at least one animal-source food and either pulses or nuts/seeds and food items from two or more of the fruit/vegetable food group. The MDD-W would be assessed using a questionnaire model (**Annex 7**) and following the guidelines by the FAO. This questionnaire will be conducted and filled in by the health professional.

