### 8.2 Variables of interest

After the termination of the study, the primary and secondary outcomes will be evaluated for normality by the Kolmogorov-Simonov test and visual inspection of histograms. In case of non-normally distributed outcomes, log transformation and non-parametric tests will be considered.

The primary outcome (healthy lifestyle questionnaire score) will be a variable with ordinal values ranging between 14-65 points. The secondary outcomes of anthropometrics (weight [kg], height [m], BMI [kg/m^2], waist circumference [cm]), clinical indicators (glycemia [mg/dL] and blood pressure [mmHg]), and total MET-min/week and kcal/week collected by the physical activity questionnaire will be variables with continuous values. Only the outcome of diet diversity will be provided as an ordinal variables ranging from 0-10.

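### Four items of the primary questionnaire (Q7, Q8, Q12, Q14) have overlapping or missing response options worth one point each, and the diet diversity cut-off contradicts its own definition

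*Combined protocol and SAP*

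**What the plan says.** The primary outcome is the sum of 14 closed questions (Annex 1), scored with the weights in Annex 6 to give 14 to 65 points.

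- **Q14, minutes per exercise session.** Options B, C and D read "B) 30–40 minutes", "C) 20–30 minutes" and "D) 20–10 minutes".
- **Q7 and Q8, fruit and vegetables; legumes and greens.** Both use the same five options. A is at every main meal and B is at least once a day. C is "C) 3 à 4 fois par semaine", D is once a week and E is less than once a week.
- **Q12, eating away from home.** A is more than three times a week and B is "B) Plus d'une fois par semaine". C is twice a month, D once a month and E less than that.

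Section 4.4 states that the trial is not blinded. Section 5.3 has the health professional ask the questions and write down the answers. Table 1 in section 5.1 lists the participant as the person administering this questionnaire, and section 8.3.6 has staff check forms that participants have completed.

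For diet diversity, section 5.3 defines the indicator as "whether participants have consumed at least five out of ten defined food groups the previous day". A few lines later it says "The threshold of this tool is: > 5 groups of food groups consumed indicates better micronutrient adequacy". Section 2.2 treats the outcome as dichotomous, while section 8.2 says "Only the outcome of diet diversity will be provided as an ordinal variables ranging from 0-10".

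**The concern.** A closed questionnaire gives a reproducible score only if every answer has exactly one place to go. Here several plausible answers have two places or none, and whoever fills in the form must choose. Under section 5.1 the data collectors are recruited from individual centres, so each works in one arm only, and they know which arm it is. With three centres per arm, a local habit of rounding up or down can line up with treatment.

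A blank is unlikely to expose the problem. Sections 5.3 and 8.3.6 have forms checked for completeness and missing answers requested. Only the chosen option goes into the Excel template, so the ambiguity could not easily be recovered later.

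For diet diversity, the two wordings of the cut-off place a woman who ate exactly five groups on opposite sides.

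**Working it through.** **1. The plan's own figures.** Every item in Annex 6 has a minimum of 1, so the lowest score is 14. Twelve items have a maximum of 5, Q1 of 2 and Q12 of 3: 12 × 5 + 2 + 3 = 65. The stated range is reproduced.

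Sections 4.3 and 8.4 give 40 analysed women per cluster, three clusters per arm, ICC 0.1, SD 7, a 6-point difference and a one-sided 5% test.
- Design effect = 1 + (40 − 1) × 0.1 = 4.9.
- Standard error = 7 × √(2 × 4.9 / 120) = 2.00.
- Power = Φ(6 / 2.00 − 1.645) = 0.912, against the stated 91%.

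**2. Item by item.** In whole counts, Q2–Q6, Q9–Q11 and Q13 have exclusive and exhaustive options. Q1 has nothing below three times a day, but its options C to E all score 2, so choosing among the nearest options changes nothing. Four items remain:

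| Item | Answer | Candidate options (points) | Difference |
|---|---|---|---|
| Q7, Q8 | every main meal | A (5) or B (4) | 1 |
| Q7, Q8 | 5–6 times a week | none; between B (4) and C (3) | 1 |
| Q7, Q8 | twice a week | none; between C (3) and D (2) | 1 |
| Q12 | more than 3 times a week | A (1) or B (1) | 0 |
| Q12 | once a week or 3 times a month | none; between B (1) and C (2) | 1 |
| Q14 | exactly 30 minutes | B (4) or C (3) | 1 |
| Q14 | exactly 20 minutes | C (3) or D (2) | 1 |

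The ceiling for one woman at one visit is 1 (Q7) + 1 (Q8) + 1 (Q12) + 1 (Q14) = 4 points. That is 4/51 = 7.8% of the width of the scale.

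**3. What this could do to a comparison of arms.** The documents give no frequency of ambiguous answers, so this is an assumption shown over a range. Suppose a share f of women is ambiguous on each of the four items, and every such answer is scored up in the intervention arm and down in the comparison arm. The mean shift is 4 × f. With no true effect, the probability of rejection is Φ(4f / 2.00 − 1.645).

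| f | Mean shift (points) | Rejection at nominal 5% |
|---|---|---|
| 10% | 0.4 | 7% |
| 25% | 1.0 | 13% |
| 50% | 2.0 | 26% |

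These are worst-direction figures. If ambiguous answers are equally common and are resolved alike in both arms, the shift is zero.

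**4. Diet diversity.** A threshold above five means six or more groups. The definition, repeated in the same section, means five or more. The two differ only for women with exactly five groups, and the documents do not say how many there are. If the 0–10 count in section 8.2 is what enters the model in section 8.3.4, the cut-off plays no part in that model. It matters only for the dichotomous indicator in section 2.2, and section 8.3.4 names a model only for ordinal and continuous outcomes.

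**The case against.** A reader might set 4 points against the 6-point target and infer that interviewers could produce two thirds of the effect. The documents do not support that. Four points needs one woman to be ambiguous on all four items at one visit, whereas 6 points is a difference between arm means. Bias also requires resolution, or the frequency of ambiguous answers, to differ by arm. A habit that stays constant within a centre would largely cancel in the planned comparison of baseline with follow-up. This stands, with one qualification. Only the intervention arm has exercise sessions and activity goals, and section 1.1 cites sessions of 30–60 minutes. If the programme moves women to 30 minutes, ambiguous answers could become commoner in that arm at follow-up and would not cancel.

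It is also not settled that an interviewer makes the choice: section 5.3 says so, but Table 1 and section 8.3.6 point to the participant. Self-completion would weaken the interviewer mechanism, but the options would stay ambiguous and the women themselves are unblinded.

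The plan promises SOPs for each measurement, training and a scoring template, where a coding rule could sit. No rule is shown, and an SOP does not alter a printed form whose options overlap. The validated source questionnaire cannot be seen, so whether these options are the validated ones is unknown.

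On diet diversity, the stray threshold reads like a slip, since the rest of section 5.3 consistently says five or more. A reader might infer that a large share of women will be misclassified, or that section 8.2's analysis is affected. The documents give no distribution of food groups, and the 0–10 analysis does not use the cut-off.

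**Conclusion.** The defects are in the text and should be corrected, because the primary outcome is scored without blinding and the correction is cheap. Four items each leave a one-point choice for certain answers. The mean shift between arms would be below the 4-point individual ceiling. Under worst-direction resolution it would be 0.4 to 2.0 points if 10% to 50% of women were ambiguous on each item; those shares are assumptions. The documents show that arm-dependent scoring is possible, not that it will happen.

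The diet diversity contradiction is smaller. It concerns a secondary outcome and bears only on the dichotomous indicator. The plan needs one cut-off and one variable type; nothing in the documents dictates a particular model for the binary version.

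**What to change.** Before baseline, with the Annex 6 points and the 14–65 range unchanged:

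- **Q14:** more than 40, 30–40, 20–29, 10–19 and less than 10 minutes.
- **Q7 and Q8:** word B as at least once a day but not at every main meal, and assign twice a week and five to six times a week each to one named adjacent option.
- **Q12:** assign once a week and three times a month to one named adjacent option.
- **All centres:** use the same form and coding rule at every centre and at all five visits.
- **Completion of the form:** reconcile Table 1, section 5.3 and section 8.3.6 on who fills it in.
- **Diet diversity:** change the threshold sentence in section 5.3 to at least five groups, and reconcile sections 2.2 and 8.2 on whether the outcome is dichotomous or a 0–10 score. If the binary indicator is kept for analysis, name a model for it.

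The cost is one revision of the form, a coding rule and a few lines of protocol text. The downside is a small further departure from the source questionnaire, which the plan has already adapted (section 2.1) and re-weighted (section 5.3).

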## Annex 2. Timeline of the study

|                          |  | 2020 |    |    | 2021 |    |    | 2022 |    |    | 2023 |    |    |
|--------------------------|--|------|----|----|------|----|----|------|----|----|------|----|----|
| Phase                    |  | T1   | T2 | T3 | T1   | T2 | T3 | T1   | T2 | T3 | T1   | T2 | T3 |
|                          |  |      |    |    |      |    |    |      |    |    |      |    |    |
| Ethical Clearance        |  |      |    |    |      |    |    |      |    |    |      |    |    |
| Preparation of tools     |  |      |    |    |      |    |    |      |    |    |      |    |    |
| Training                 |  |      |    |    |      |    |    |      |    |    |      |    |    |
| Recruitment              |  |      |    |    |      |    |    |      |    |    |      |    |    |
| Intervention             |  |      |    |    |      |    |    |      |    |    |      |    |    |
| Evaluation               |  |      |    |    |      |    |    |      |    |    |      |    |    |
| Data analysis            |  |      |    |    |      |    |    |      |    |    |      |    |    |
| Dissemination of results |  |      |    |    |      |    |    |      |    |    |      |    |    |

**Annex 3. Intervention components and topics covered by T2DM and GD preventive intervention program**

| Intervention components                                    | program | Topics                                                                                                                                                                                                                                                                                                             |
|------------------------------------------------------------|---------|--------------------------------------------------------------------------------------------------------------------------------------------------------------------------------------------------------------------------------------------------------------------------------------------------------------------|
| Individualized education (both groups)              |         |                                                                                                                                                                                                                                                                                                                    |
| Dietary advice based on dietary needs of DRC  | -       | Food groups and food sources
Food choices: WHO healthy diet guidelines  considering the Congolese food and cultural profile: dietetic consultation guideline 
Plate distribution; adapted to foods frequently consumed in Kisantu 
A healthy diet during pregnancy |
| Physical activity                                          | -       | WHO physical activity advice and examples 
Physical activity during pregnancy                                                                                                                                                                                                         |
| Educational material                                       | -       | Topics above.                                                                                                                                                                                                                                                                                                      |
| Group education (intervention group)                |         |                                                                                                                                                                                                                                                                                                                    |
| T2DM and GDM                                  | -       | Definition of T2DM and GDM
Complications
Prevention                                                                                                                                                                                                                                                          |
| Benefits of physical activity                 | -       | Weight control
Prevention of NCDs                                                                                                                                                                                                                                                                               |
| Cooking oils and preparation techniques                    | -       | Cooking methods
Cooking oils
Benefits and risks
Example of healthy cooking methods                                                                                                                                                                                                                        |
| Alcohol and tobacco use                                    | -       | Risks of excessive use                                                                                                                                                                                                                                                                                             |
| Healthy weight gain during pregnancy                       | -       | Benefits and risks
How to reach a healthy weight gain                                                                                                                                                                                                                                                           |
| Educational material                                       | -       | Topics above.                                                                                                                                                                                                                                                                                                      |
| Physical activity classes (intervention group)      |         |                                                                                                                                                                                                                                                                                                                    |
| Work-out sessions                                          | -       | Walking pathway
Aerobics class
Dancing class                                                                                                                                                                                                                                                                 |
| Setting goals (intervention group)                  |         |                                                                                                                                                                                                                                                                                                                    |
| Personal goals                                             | -       | Setting individualized dietary goals
Setting weight goals
Setting physical activity goals                                                                                                                                                                                                                    |
| Pedometer (intervention group)                      |         |                                                                                                                                                                                                                                                                                                                    |
|                                                            | -       | Individual explanation (incorporated to the individual component): How to use a pedometer
Use a pedometer                                                                                                                                                                                                       |
| Community based activities (intervention group)     |         |                                                                                                                                                                                                                                                                                                                    |
| Community activities                                       | -       | Sharing cooking recipes
Physical activity classes
Educational class with family
Sharing personal journey                                                                                                                                                                                                  |

**Annex 6. Lifestyle questionnaire score weighted answers**

| Question | Answers |   |   |   |   |
|----------|---------|---|---|---|---|
|          | A       | B | C | D | E |
| Q1       | 1       | 1 | 2 | 2 | 2 |
| Q2       | 1       | 2 | 3 | 4 | 5 |
| Q3       | 1       | 2 | 3 | 4 | 5 |
| Q4       | 1       | 2 | 3 | 4 | 5 |
| Q5       | 1       | 2 | 3 | 4 | 5 |
| Q6       | 1       | 2 | 3 | 4 | 5 |
| Q7       | 5       | 4 | 3 | 2 | 1 |
| Q8       | 5       | 4 | 3 | 2 | 1 |
| Q9       | 1       | 2 | 3 | 4 | 5 |
| Q10      | 1       | 2 | 3 | 4 | 5 |
| Q11      | 1       | 2 | 3 | 4 | 5 |
| Q12      | 1       | 1 | 2 | 2 | 3 |
| Q13      | 5       | 4 | 3 | 2 | 1 |
| Q14      | 5       | 4 | 3 | 2 | 1 |

|           |    |
|-----------|----|
| Min score | 14 |
| Max score | 65 |

